### Methods in analysis to handle protocol non-adherence and any statistical methods to handle missing data {20c}

The study will be analyzed according to the intention to treat principle. All data that is collected is from the LTC inteRAI form and data entry is mandated by the province. We do not expect missing data.

### Plans to give access to the full protocol, participant-level data, and statistical code {31c}

The full protocol will be published online and anonymize participant-level data will be made available upon request to the principal investigator ([name]). Data will be made available for 1 year following the publication of the primary manuscript from the trial.

### Outcomes {12}

The co-primary outcomes of interest are:
The effectiveness of MedReviewRx for deprescribing based on the proportion of participants with one or more PIMs deprescribed, compared to usual care.Feasibility of the intervention (see below for complete definition).

#### Impact on PIMs

The impact on PIMs will be determined by the proportion of nursing home residents who have one or more PIMs reduced or stopped after the treating physician receives a MedSafer report. This outcome will be measured by using unique identifiers to compare medication data from sequential interRAI data sets. PIMs identified in the baseline data set will be compared with the next data set (3 months later) transmitted with that unique identifier to determine if any of the PIMs has been stopped (no longer listed) or if a PIM dose has been reduced. This process will continue for the study duration. All statistical comparison will be performed via STAT v 15 (or equivalent) and the stepped wedge function will be used for the primary outcome (proportion of patients with one or more PIMs deprescribed over the study period).

At the end of the study, subgroup analysis will be conducted on the PIM data to explore PIM use based on sex, gender, and geographic location.

Co-primary outcome:
User experience with MedSafer reports and MedReviewRx.

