**Methods:**

This study will employ a mixed methods effectiveness-implementation hybrid type 2 study design. To measure effectiveness, a stepped wedge cluster randomized trial design is planned, which allows us to approximate a randomized clinical trial. Approximately 1000 residents living in LTC will be recruited from five facilities in New Brunswick. The study will begin with 3 months of baseline data on rates of deprescribing. Thereafter, every 3 months a new cluster will enter the intervention mode. The intervention consists of medication reviews augmented with the MedReviewRx software, which will be used by staff and clinicians in the facilities. The estimated study duration is 18 months and the main outcome will be the proportion of patients with one or more PIMs deprescribed (reduced/stopped or changed to a safer alternative) in the 90 days following a prescription review. The goal is to study the impact of MedReviewRx on medication overload among older adults living in LTC. In typical fashion of a stepped wedge cluster randomized trial, each cluster acts as an internal control (before and after) as well as a control for the other clusters (external control). Qualitative data collected will include resident/caregiver attitudes towards deprescribing and semi-structured interviews with staff working in the long-term care homes.

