#### Variables under investigation include:

A)Patient demographics (date of admission to LTC, age, sex, gender, nursing home identifier, medical, and psychiatric conditions documented in the interRAI LTCF assessment, and date of discharge from LTC if applicable).B)Medication use data: absolute number of medications, number of PIMs, proportion of all medications that are PIMs, and type of deprescribing opportunities identified (PIMs that are high risk, intermediate risk, or of little added value).C)Safety data: death, fracture, fall, use of restraints, transfer to hospital, change in functional status based on interRAI activities of daily living (ADL) scores. Episodes of delirium based on responses to questions in Section C of the interRAI LTCF assessment form (periodic disordered thinking or awareness and acute change in mental status from a person’s usual functioning).D)D)Health care provider experience with MedReviewRx and MedSafer deprescribing information as described in the user feedback surveys and the acceptability and feasibility survey.E)Nursing home evaluation of the implementation toolkit.F)Patient and caregiver attitudes about deprescribing.

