Our study has limitations. Our sample profile represents only a subset of New Brunswick nursing homes. Data from nursing homes in other provinces and other countries would provide a broader, diversified perspective to the current polypharmacy landscape. Our intervention may not apply to provinces and countries where medication reviews are not mandated, or in the absence of a unified electronic medical record for nursing home residents. Increased funding for a prolonged study period (lasting multiple years) would allow us to collect more data on the sustainability of the intervention. Finally, a larger sample size would increase our power to detect a difference in more rare outcomes such as preventable hospitalizations and death.

That said, the study has several advantages. For healthcare professionals, providing deprescribing reports will bring greater awareness to the risks of polypharmacy and PIMs. The convenience of easily accessing the reports online should also facilitate the process of deprescribing, rendering it more scalable. And while residents may not always be aware that their health care professional is using MedReviewRx to assess their medication regimen, they stand to benefit directly from the intervention through deprescribing medications that could be harmful, or of little added value. The result for the patient should be a decreased medication burden. Finally, from a health services perspective, we expect time savings for the pharmacy team by partly automating the medication review process.

In conclusion, this study will provide valuable information on PIM use as well as facilitators and challenges associated with medication reviews and deprescribing. We hope that this study will demonstrate that implementing MedReviewRx is feasible and acceptable to health care providers in NBNHs and that it results in a decreased PIMs and cost savings. This study is an important step towards understanding and promoting tools to guide safe and rational reduction in PIM use among older adults. We believe that MedReviewRx will be an efficient, user-friendly application that will be very useful to physicians, pharmacists, and nurses and will greatly facilitate the deprescribing process.

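### The primary responder rule counts a swap from one PIM to another as a stop, and no net PIM or medication count is a defined outcome, so the primary result alone cannot show that PIM burden fell

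*Protocol article*

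**What the plan says.** Outcomes {12} sets the effectiveness co-primary outcome "based on the proportion of participants with one or more PIMs deprescribed, compared to usual care". The section Impact on PIMs makes it operational: "PIMs identified in the baseline data set will be compared with the next data set (3 months later"), and the purpose is "to determine if any of the PIMs has been stopped (no longer listed) or if a PIM dose has been reduced". The process repeats each quarter.

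The abstract words the same outcome as the "proportion of patients with one or more PIMs deprescribed (reduced/stopped or changed to a safer alternative) in the 90 days following a prescription review". It also states the aim: "The goal is to study the impact of MedReviewRx on medication overload among older adults living in LTC". The Discussion hopes to demonstrate that "it results in a decreased PIMs and cost savings".

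The data to be collected include "absolute number of medications, number of PIMs, proportion of all medications that are PIMs" (Variables under investigation). None of these counts is named as a primary, secondary or tertiary outcome. Project evaluation mentions looking at how PIM use changes overall, but gives no measure and no comparison of intervention with control.

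**The concern.** The look-up runs in one direction, from the earlier PIMs to the later list. It asks what has gone or been lowered, and never what has arrived. Two consequences follow.

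- A PIM replaced by another flagged PIM is scored as stopped, because the first is no longer on the list. The abstract's wording for changes, which refers to a safer drug, has no counterpart in the operational rule.
- A resident with one dose reduction and new PIMs added is a success although the number of PIMs has risen.

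At stake is what a positive primary result can be said to mean. It would show that more residents had some PIM stopped or reduced. It would not by itself show that residents carried fewer PIMs or fewer medications, which is what the goal and the hoped-for conclusion refer to. The counts that would show this are extracted each quarter but have no defined role in the comparison.

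**Working it through.** **1. The rule applied to simple cases** (letters are MedSafer-flagged PIMs)

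| Earlier list | Next list | Scored under Impact on PIMs | Change in PIM count |
|---|---|---|---|
| A, B | B | success | -1 |
| A, B | B, C | success | 0 |
| A, B | B, C, D | success | +1 |
| A, B | A at lower dose, B, C, D | success | +2 |

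All four are scored alike. Only the first is a net reduction.

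**2. The plan's own power figure.** Inputs from Sample size {14}: 10% versus 20%, 175 residents with a PIM per cluster, cluster autocorrelation (CAC) 0.8, ICC 0.05 or 0.02. From the participant timeline: 3 clusters, 4 periods. Recruitment {15} gives a closed cohort. Assumed, because not stated: two-sided alpha 0.05 and individual autocorrelation (IAC) 0.8.

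- v = mean of p(1-p) = (0.09 + 0.16)/2 = 0.125
- s = v·ICC·(1-CAC) + v·(1-ICC)·(1-IAC)/175
- t = v·ICC·CAC + v·(1-ICC)·IAC/175
- For this layout, Var(effect) = 3s(s + 4t)/(4s + 10t)

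ICC 0.05: s = 0.001386, t = 0.005543, SE = 0.0401, power = Φ(0.10/0.0401 - 1.96) = 70.4%.
ICC 0.02: s = 0.00064, t = 0.00256, SE = 0.0272, power = 95.7%.

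The article states 72% and 96%, so both figures reproduce to within 2 points and are not in question.

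**3. What offsetting would do.** Net rate = gross rate × (1 - share of successes offset by another PIM). No share is given in the document. Every share below is an assumption.

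| Share offset, control / intervention | Net rates | Difference | NNT |
|---|---|---|---|
| 0 / 0 (as planned) | 10% vs 20% | 10 points | 10 |
| 25% / 25% | 7.5% vs 15% | 7.5 points | 13 |
| 50% / 50% | 5% vs 10% | 5 points | 20 |
| 20% / 40% | 8% vs 12% | 4 points | 25 |
| 20% / 60% | 8% vs 8% | 0 | none |
| 0 / 50% | 10% vs 10% | 0 | none |

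In every row the rule as written still reports 10% versus 20%. Equal shares shrink the difference but keep its direction and the doubling of the rate. The two zero rows were chosen to cancel exactly, so they show what is possible and not what is likely.

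**4. Power if a net rule were primary** (same design and assumptions; SE scales with the square root of v). For 7.5% versus 15%, v = (0.0694 + 0.1275)/2 = 0.0984 and SE = 0.0401 × √(0.0984/0.125) = 0.0356. Power = Φ(0.075/0.0356 - 1.96), about 56% at ICC 0.05, and 87% at ICC 0.02. With a 50% equal offset (5% versus 10%), power is 39% and 70%.

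**The case against.** The best defence is that the outcome answers the question asked. Research questions and Objectives speak of deprescribing PIMs, and the data monitoring section calls the trial a study of process and implementation. A responder measure of deprescribing is valid for that, and the sentence on decreased PIMs is expressed as a hope. This stands. It limits the point to what the outcome can support beyond deprescribing activity. The abstract, however, states the goal as an effect on medication overload, so the gap is real.

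Second, usual care also contains switches and new starts, and the comparison is with usual care. This also stands: turnover in equal proportion does not create or reverse a difference. A reader might infer that the app is likely to increase PIM-for-PIM switches. The documents do not say so. They describe reports that identify PIMs, explain the reason, give tapering instructions and link to non-drug material, and the analysis is rerun every 3 months, so a replacement PIM could itself be flagged. Whether switching differs between phases is unknown.

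Third, the abstract's wording is a list of alternatives. A stopped PIM already qualifies, and the change to a safer drug is one more route. A reader might infer that the abstract expressly bars a swap; it does not. What remains is that the two definitions differ and that neither says how a swap is scored.

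Fourth, a reader might infer that cost savings would be overstated too. Tertiary outcomes bases costing on medication prices and dispensing fees and does not tie it to the responder rule, so that inference has no support.

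Finally, an analysis plan that is not shown may add a net measure. The outcome definition fixed in this article does not.

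**Conclusion.** The point holds in a limited form. As written, the rule scores a PIM-for-PIM swap as a stop and ignores PIMs that are added. The two definitions of the primary outcome do not match, and no net PIM or medication count has a defined intervention-control comparison. The rule is sound as a process measure, but a positive result on it would not by itself show less medication overload or fewer PIMs.

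The size cannot be estimated from the document. Under assumed equal offsetting of 25%, the planned 10-point difference would be 7.5 points net. It disappears only under assumed shares that are much higher in intervention quarters. A reader might go further and conclude that the trial is set to report a false success; that needs differential swapping, for which the document gives no evidence.

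**What to change.** 1. Reconcile the abstract with Impact on PIMs, so that a PIM replaced in the next data set by another MedSafer-flagged PIM for the same purpose is not counted as stopped. If the present rule is kept as primary, make this a pre-specified sensitivity analysis of it. Fix how drugs are grouped by purpose before outcome data are seen. This concerns scoring only, not prescribing.
2. Name net change in number of PIMs and in number of medications per resident-quarter as secondary outcomes, analysed in the same stepped-wedge comparison with a model suited to counts. This also captures new PIMs for other purposes, which the first change would miss.

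The cost is one extra condition in the outcome program and two more analyses, with no new data collection. If the stricter rule is made primary, event rates and power fall: to about 56% at ICC 0.05 with a 25% equal offset and the assumed individual autocorrelation of 0.8, against the stated 72%. Using it as a sensitivity analysis avoids that loss.

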#### User experience

User experience with MedSafer reports and MedReviewRx will be measured using survey responses as well as described through interview data and informal feedback received by the study team. Several outcomes will be studied: how satisfied the user is with the App, including how helpful they find it, the added knowledge from a MedSafer report for the prescriber, how likely the prescriber is to continue using the App once the study is over. Survey responses will be analyzed based on the following themes: value and benefits, scientific content, and user satisfaction. Interview data will be thematically analyzed [16].

Secondary outcomes to be examined at 90 days following each intervention cycle include:
A)Although we are not powered to show a reduction in other outcomes, we will explore any impact of the intervention on reduction of fractures, falls, use of restraints, transfer to hospital, change in functional status (based on interRAI activities of daily living (ADL) scores), episodes of delirium (based on responses to questions in Section C of the interRAI LTCF assessment form: periodic disordered thinking or awareness) and death.

#### Tertiary outcomes include:

A)Cost savings analysis related to cost saved from medications (actual price of the medication as well as dispensing fees) balanced with the cost of deployment of MedSafer including maintaining the program with updates and user support.B)Patient and family attitudes about deprescribing will be reported using survey responses collected from the rPATD questionnaires.

#### Project evaluation

This project will be evaluated locally at each participating nursing home site to determine usability, impact on workflow, time commitment, and value added. Qualitative and quantitative user feedback as described above will be used to explain study findings.

Patient and family attitudes about deprescribing will be described descriptively using survey responses collected from the revised rPATD questionnaires.

An analysis will be conducted to determine strategies to inform widespread deployment, nursing home evaluation of the implementation toolkit, prescribing patterns based on geographic area and overall change in PIM use. System-level impact on cost savings and cost avoidance of adverse effects will be projected.

### Study setting [9]

A subset of nursing homes in New Brunswick have agreed to participate in the study. Study participants will include health care providers and nursing home staff at participating nursing homes, as well as the older adults who live in these nursing homes and their family members or substitute decision makers.

Our study represents a total 804 nursing home beds and will provide a sample of NBNH residents and health care providers in three urban centers representing both large and mid-size long-term care facilities who conduct business in English, as well as one long-term care facility being bilingual (English and French).

### Eligibility criteria [10]

#### Inclusion criteria

Residents residing in one of the participating homesAged 65 years of age or olderTaking one or more PIMs (as identified by MedSafer)

#### Exclusion criteria for the secondary outcome of attitudes towards deprescribing

If both the patient and proxy are unable to complete the survey, the patient will be excluded from the survey component of the study.

### Participant timeline {13}

**Table Tabb:** 

	Study period						
	Allocation^**1**^	Post-allocation				Follow-up data	Close-out
Timepoint	***0***	***Months 1–3***	***Months 4–6***	***Months 7–9***	***Months 10–12***	***Months 13–15***	***Months 16–18***
**Enrolment**							
Eligibility screen	X						
Informed consent	X						
**Control (C) Intervention (I)**							
Cluster 1		C	I	I	I		
Cluster 2		C	C	I	I		
Cluster 3		C	C	C	I		
**Assessments**							
Demographic data		X	X	X	X	X	
Medication data		X	X	X	X	X	
Safety data		X	X	X	X	X	
Nursing Home Site Assessment Questionnaire		X					
RPATD^**2**^ Questionnaire: Older Adult Version		X					
RPATD^2^ Questionnaire : Caregiver Version		X					
User Feedback Survey			X		X		
Acceptability and Feasibility Survey						X	
Implementation Evaluation Interview			X	X	X		
End Of Study Feedback Interview					X		
**Data analysis**						X	X

^1^As this is a cluster randomized controlled trial, allocation occurs at the cluster level

^2^*RPATD* Revised Patient Attitude Towards Deprescribing

### Who will take informed consent? (26a)

A waiver of informed consent for participation in the deprescribing intervention aspect of the study as well as for secondary use of data was obtained from the research ethics board of the Horizon Health Network Research Ethics Board. Informed consent for participation in the survey component of the study will be obtained at the time of survey completion with a preamble prior to any survey completed. Residents who are unable to provide informed consent for surveys will have a surrogate decision maker approached when available. All residents regardless of capacity to consent are eligible for the quality improvement intervention due to a waiver obtained from the research ethics board.

Additional consent provisions for collection and use of participant data and biological specimens {26b}

Not applicable. No biological specimens will be collected as part of this trial.

### Explanation for the choice of comparators {6b}

Deprescribing using MedReviewRx during the intervention phase will be compared with usual care (deprescribing when not using MedReviewRx) in the control phase.

Prescribers (physicians and nurse practitioners) and pharmacists providing care at the study nursing homes will be eligible to use MedReviewRx to conduct prescription check-ups for older adults under their care. Nursing home staff (unit clerks, administrators, interRAI coordinators, and nurses) at the study site will be eligible to register to load LTCF assessment information into MedReviewRx and print MedSafer reports from the system for prescribers who do not use MedReviewRx. A designated contact person will be appointed by the Director of Nursing or designate at each nursing home. The study site contact will act as a liaison with the research study team and coordinate study site activities. Study site contacts will also complete a site assessment questionnaire at the beginning of the study and an interview within 3 months of initial MedReviewRx implementation. Prescribers, pharmacists, nurses, and staff at study nursing homes will be recruited to complete surveys to evaluate the MedReviewRx system and MedSafer report information. At the end of the study site contacts, nursing home staff, prescribers, pharmacists, and nurses will be recruited to participate in an interview to evaluate the program. Consent will be obtained for MedReviewRx users, interview, and survey participants.

Adults aged 65 years or older who live at participating nursing homes and have had a quarterly interRAI LTCF assessment completed are eligible for MedSafer analysis. A waiver of patient consent was requested and approved to load patient data into MedReviewRx. InterRAI LTCF assessments are completed on admission to a NBNH, and every 3 months thereafter as a standard of care. Assessment data is collected by NBNHs electronically using Momentum software. Momentum has written a customized data extract report for this project. Patient demographics, medical conditions, medication information, and safety monitoring data required for this study are extracted from the Momentum extract report and uploaded into MedReviewRx at the study site. MedReviewRx removes identifiable patient information and assigns a unique identifier to each person’s data set, and anonymized data sets are encrypted and securely transmitted to MedSafer for analysis. The ability to download secondary interRAI assessment data on medical conditions, medication lists, and safety data for each nursing home resident is essential to this research study. Without this information, it will not be possible to calculate the proportion of PIMs used at the study sites, evaluate the impact of MedReviewRx on deprescribing at each site, or assess study safety endpoints. A waiver of consent is unlikely to adversely affect the welfare of individuals to whom the information relates as the information is already collected as part of usual care. Study researchers have conducted an analysis of the MedReviewRx system and appropriate measures have been taken to protect the privacy of individuals and to safeguard personal health information. It is impracticable to seek consent from all individuals to whom the secondary information relates as new nursing home residents are admitted regularly when previous residents are discharged or deceased, interRAI data is downloaded in batches by assessment date, and study endpoints require information on all residents in each study site. In addition to safeguarding information, the research team will enter into data sharing agreements with each study site to obtain permission for secondary use of information for this research study.

Adults aged 65 years or older who live at a participating nursing home during the study, and their family members or substitute decision makers will be recruited to participate in a survey to explore their attitudes on medication use and deprescribing. Posters will be placed in study nursing homes; the study will be promoted verbally at resident and family council meetings and a recruitment communication will be sent by email or mail to family members identified as contacts and/or substitute decision makers in the resident’s admission documents. Consent will be obtained for survey completion.

